### Sample size estimation

2.9

The two integrated components of this mixed-design study underwent separate sample size estimations. Calculations were conducted using PASS software (version 16.0, NCSS, Kaysville, Utah, USA), and a 20% attrition rate was accounted for in both calculations.

For the matched case–control observational component, the sample size was estimated based on expected differences in ABR wave V latency, which was selected as the primary electrophysiological endpoint for this comparison. Based on preliminary observations from an exploratory pilot assessment, a mean paired difference in wave V latency of 0.08 ms with a standard deviation of the differences of 0.14 ms was assumed. The preliminary assessment was primarily designed to evaluate the feasibility of ABR measurement and estimate potential differences in ABR parameters between tinnitus participants and healthy controls. Using a paired-sample t-test with a two-sided α level of 0.05 and a statistical power of 80%, a minimum of 30 matched pairs (60 total participants) is required. Accounting for a 20% attrition rate, 36 pairs (72 total participants: 36 patients and 36 matched healthy controls) will be recruited.

For the self-controlled interventional component (within the patient group), the sample size was calculated based on anticipated changes in the Tinnitus Handicap Inventory (THI) score, which serves as the primary clinical endpoint for evaluating treatment efficacy. Based on our pilot study and previous clinical observations (35), a mean reduction in THI score of 12.07 points with a standard deviation of 23.28 points after treatment is anticipated. We acknowledge that this standard deviation is relatively large compared to the estimated mean change, which reflects the substantial clinical heterogeneity inherent in chronic tinnitus patients with respect to baseline symptom severity and psychosocial comorbidities. Notably, however, our final target of 36 patients is considerably larger than the minimum required sample size of 24 derived from these pilot estimates. This conservative oversampling strategy enhances the robustness of the study against data overdispersion and potential outliers, and ensures adequate statistical power for detecting the hypothesized treatment effect even with a moderate effect size. For a paired-sample *t*-test (α = 0.05, two-sided; power = 80%), 24 patients are required. To align with the sample size of the case–control component and to account for potential attrition, the final target for the patient group is set at 36 participants.

Thus, a total of 72 people will be included in the study sample: 36 patients with chronic tinnitus and 36 healthy controls who are matched for age and sex. This sample size ensures sufficient statistical power for both the between-group comparisons at baseline and the within-patient longitudinal analysis of treatment effects.

It should be noted that, although the primary longitudinal analysis will employ a two-way mixed-design analysis of variance (ANOVA) to evaluate the group × time interaction effect, the sample size calculations were conservatively based on simpler t-test frameworks (paired t-test for the matched baseline comparison, and paired t-test for the within-patient pre-post comparison). This approach is methodologically standard in clinical trial planning for the following reasons. First, sample size estimation is conventionally anchored to the most clinically meaningful single contrast to ensure adequate power for detecting the minimal effect of interest, without requiring assumptions about the covariance structure among repeated measurements. Second, mixed-design ANOVA generally provides equal or greater statistical power than pairwise *t*-tests for detecting time-related changes, as it accounts for the correlation structure among repeated measurements and pools variance more efficiently. Third, with 36 participants per group, the study is adequately powered not only for the primary t-test-based comparisons but also for the mixed ANOVA interaction test; post-hoc power calculations based on a moderate effect size (*f* = 0.25) for the group × time interaction indicates that 36 participants per group provide >85% power at α = 0.05 with two groups and two time points. Therefore, the sample sizes derived from the t-test assumptions represent a conservative lower bound that guarantees sufficient power even under the simplest analytical framework, while the subsequent application of mixed-design ANOVA will further enhance the sensitivity to detect the group × time interaction effect without compromising the validity of the study.

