In addition, although the following measures will not reduce the placebo effect, we will take further steps to ensure the overall scientific rigor and interpretability of the study results. Baseline characteristics of all participants will be compared to verify the comparability between the tinnitus and healthy control groups. During recruitment, participants will be provided with standardized information regarding the study procedures, potential benefits, possible adverse reactions, and the sensory experiences associated with acupuncture. The information will be presented in a balanced manner to ensure adequate understanding of the intervention without emphasizing potential treatment outcomes. Furthermore, subjective questionnaire data will be evaluated alongside objective ABR measures to provide complementary information regarding clinical changes and associated neurophysiological alterations. The Standard Protocol Items: Recommendations for Interventional Trials (SPIRIT) guidelines will be followed in the development of the protocol (29). Zhejiang Chinese Medical University’s Third Affiliated Hospital will host the study. A total of 72 participants will be included in this study, including 36 patients with chronic tinnitus and 36 healthy controls who matched the patient in age and sex. Healthy controls will be individually matched with tinnitus participants according to sex and age within ±3 years. In addition to demographic matching, we will also compare PTA and audiogram characteristics between the two groups at baseline, as well as before and after treatment within each group. If there are significant intergroup differences in audiogram characteristics, these specific frequencies will be included as covariates in the statistical model used to compare auditory brainstem response (ABR) parameters between groups. The treatment plan includes 10 sessions of acupuncture, which can be completed within 4 weeks and carried out three times a week (usually 2 days apart between each treatment). There are three time points used to evaluate tinnitus-related clinical outcomes and auditory brainstem response (ABR) parameters, namely the baseline period (before the start of treatment), the end of the course (within 1 week after the tenth treatment), and the 8th week after the completion of treatment as follow-up point. The Institutional Ethical Review Board (IRB) of the Third Affiliated Hospital of Zhejiang Chinese Medical University has granted ethical permission for the trial (ZSLL-KY-2025-032-01), which will be conducted in accordance with the Declaration of Helsinki. The Ethics Committee will be notified right away of any amendments to the study design. NCT07522567 is the identification code for this trial’s registration in the Clinical Trials Registry. Table 1 displays the study’s SPIRIT list, while Figure 1 displays the flow diagram.

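### Case-control sample size: the stated minimum (30 pairs), attrition (20%) and target (36 pairs) do not fit together, and the printed inputs give 27 pairs rather than 30; power is not harmed

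*Protocol article*

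**What the plan says.** Section 2.9 (Sample size estimation) of the protocol article sizes the case-control component on wave V latency. It gives every input needed to check the result: "a mean paired difference in wave V latency of 0.08 ms with a standard deviation of the differences of 0.14 ms was assumed", analysed by a paired t-test at two-sided α 0.05 with 80% power. From these it concludes that "a minimum of 30 matched pairs (60 total participants) is required". The opening paragraph of the section says that "a 20% attrition rate was accounted for in both calculations", and the case-control paragraph ends: "Accounting for a 20% attrition rate, 36 pairs (72 total participants: 36 patients and 36 matched healthy controls) will be recruited".

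The pairing is real. Section 2.1 (Design overview) states: "Healthy controls will be individually matched with tinnitus participants according to sex and age within ±3 years". Section 2.8 (Statistical analysis) compares the groups at baseline with paired t-tests or Wilcoxon signed-rank tests. Section 2.9 then sets the patient target of the interventional component at 36, partly to align it with this calculation, so the total of 72 rests on these figures.

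**The concern.** Two steps in the paragraph do not follow from the figures printed in it.

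- **Attrition step.** A minimum of 30 with 20% attrition should lead to a target that still leaves 30 after the loss. A target of 36 does not.
- **Minimum.** A reader who enters the printed difference, SD, α and power into a paired t-test calculation does not obtain 30.

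At stake is whether the stated justification for 72 participants can be checked and is true as written. If the planned-for attrition occurred, the study would miss the requirement that it set for itself, even if that requirement is higher than the inputs call for.

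**Working it through.** **Inputs** (all from section 2.9): mean paired difference 0.08 ms; SD of differences 0.14 ms; paired t-test; two-sided α = 0.05; power 80%; stated minimum 30 pairs; attrition 20%; target 36 pairs.

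**1. The plan's own target.** 30 × 1.2 = 36 reproduces the target exactly. Multiplying by (1 + 0.20) does not offset a 20% loss:

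- Remaining after loss: 36 × (1 − 0.20) = 28.8, so 28 complete pairs, fewer than 30.
- Needed to keep 30: 30 / (1 − 0.20) = 37.5, so 38 pairs (76 people).

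This step needs no power calculation and holds however the 30 was obtained.

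**2. The plan's own minimum.** The standardised effect is d = 0.08 / 0.14 = 0.571. Exact power uses the noncentral t distribution with n − 1 degrees of freedom and noncentrality d√n:

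| Pairs | Power |
|---|---|
| 26 | 79.96% |
| 27 | 81.5% |
| 28 | 83.0% |
| 29 | 84.4% |
| 30 | 85.6% |
| 36 | 91.5% |

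The smallest number reaching 80% is 27. Thirty is the smallest number reaching 85%, a level that the protocol does not state.

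**3. Other routes to 30.**

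| Variant | Pairs |
|---|---|
| Normal approximation, ((1.96 + 0.84)/d)² = 24.04 | 25 |
| The same plus 1.96²/2 = 25.96 | 26 |
| One-sided t-test | 21 |
| α = 0.025 | 32 |
| Wilcoxon adjustment, 27/0.955 = 28.3 | 29 |

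An unpaired comparison would need 49 per group. None of these gives 30.

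**4. Rounding of the inputs.** To two decimals, 0.08 may stand for 0.075 to 0.085 and 0.14 for 0.135 to 0.145. At the extremes, 0.085/0.135 = 0.630 needs 22 pairs and 0.075/0.145 = 0.517 needs 32. For example, 0.075/0.14 = 0.536 needs exactly 30. So 30 can be reached within rounding, but the values that would give it are not shown.

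**5. Attrition applied to 27.** 27 / 0.8 = 33.75, so 34 pairs. The planned 36 exceeds this.

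**The case against.** The strongest defence has three parts.

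- **The 30 errs on the safe side.** It exceeds what the printed inputs require and may come from a software run on unrounded pilot values. This stands. The minimum cannot be reproduced from the printed figures, but it is not shown to be a miscalculation. The defence does not rescue the attrition step, however: if 30 truly is the minimum, 36 is too few to protect it against 20% loss.
- **The slips offset.** With 28 pairs left, power on the printed inputs is still 83.0%. This stands, and it is why the point is minor.
- **Attrition hardly touches this comparison.** It uses ABR recorded at T0, in week −1 of Table 1, before treatment. Dropout during the acupuncture course does not remove those recordings; only a missing or unusable baseline recording does. This stands too. But section 2.9 itself applies the 20% here, so the allowance should be computed correctly.

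Two stronger readings are tempting. A reader might infer that the baseline comparison is underpowered; the figures above show that, on the printed inputs, it is not. A reader might also reason that losing either member breaks a pair, so that 20% loss per person would shrink the retest analysis far below 28 pairs. The protocol does not support this. Section 2.8 plans no retest analysis between matched partners: the mixed ANOVA treats group as a between-subject factor, and the within-group tests pair each participant with themselves. Independent 20% loss in each member would also be an added assumption.

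**Conclusion.** The point holds as a minor internal inconsistency. The stated minimum of 30 pairs, the 20% attrition and the target of 36 cannot all stand: 36 leaves 28 complete pairs, and keeping 30 would take 38. Separately, the printed inputs give 27 pairs, not 30, a difference of 3; the 30 corresponds to about 85% power or to unrounded inputs that are not shown (22 to 32 pairs within rounding).

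The design is not damaged. On the printed inputs, power is 83.0% at 28 pairs and 91.5% at 36, both above the 80% target. This rests on the printed 0.08 ms and 0.14 ms being the intended planning values, on a paired t-test, and on the 20% being a loss of pairs. What needs correcting is the written justification, not the number recruited.

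**What to change.** Keep 36 pairs and change the wording of section 2.9 in one of two ways:

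- State that 27 pairs give 80% power on the printed inputs, and that 36 pairs leave 28 after 20% pair loss (83% power).
- If 30 is the intended minimum, state the unrounded inputs or the power level (about 85%) that produce it, and report openly that 36 pairs leave 28 after 20% loss.

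The cost is a few words in one paragraph. No extra participants are needed, and nothing changes in the procedures or the analysis.

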### Statistical analysis

2.8

Statistical analyses will be performed using SPSS version 27.0 (IBM Corp., Armonk, NY, USA). All statistical tests will be two-sided, with a significance level of *p* < 0.05. Baseline demographic and clinical characteristics will be summarized using descriptive statistics. Continuous variables will be presented as mean ± standard deviation (SD) or median (interquartile range, IQR), depending on data distribution, while categorical variables will be expressed as frequencies and percentages. Normality of continuous variables will be assessed using the Shapiro–Wilk test and visual inspection of Q–Q plots. For the control group, ABR measurements will be performed at two time points (T0 and T1, matching the interval of the patient group) to assess test–retest variability. This allows us to distinguish treatment-related changes from normal variability. For bilateral ABR measurements, the primary analysis will be conducted at the participant level by averaging measurements from both ears.

For baseline comparisons between tinnitus participants and healthy controls, paired-sample t-tests or Wilcoxon signed-rank tests will be used according to data distribution, because controls will be individually matched with tinnitus participants based on age and sex.

Longitudinal changes in ABR parameters will be analyzed using two-way mixed-design analysis of variance (ANOVA), with group (chronic tinnitus vs. healthy control) as a between-subject factor and time (baseline vs. post-treatment/retest assessment) as a within-subject factor. If significant between-group differences in audiometric profiles are detected at baseline or within each group, corresponding frequency-specific hearing thresholds will be included as covariates in the analyses. The primary parameter of interest will be the group × time interaction effect, which will determine whether changes in ABR parameters over time differ between tinnitus participants and healthy controls. If the interaction is significant, simple main effects will be examined with Bonferroni correction. Intraclass correlation coefficients (ICC, two-way random-effects model) will be calculated for each ABR parameter in healthy controls to assess test–retest reliability. Within-group changes between baseline and post-treatment/retest assessment will also be examined using paired-sample *t*-tests or Wilcoxon signed-rank tests when appropriate.

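### The 24 patients stated as sufficient for the THI outcome do not follow from the stated inputs: 32 are needed, and 36 patients with 20% attrition fall below 80% power

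*Protocol article*

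**What the plan says.** All inputs are in section 2.9 of the protocol article (Sample size estimation). For the THI, "a mean reduction in THI score of 12.07 points with a standard deviation of 23.28 points after treatment is anticipated". The test is a paired t-test ("paired t-test for the within-patient pre-post comparison"), and the result is given as "α = 0.05, two-sided; power = 80%), 24 patients are required". Section 2.8 makes two-sided testing the general rule: "All statistical tests will be two-sided, with a significance level of" 0.05.

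On attrition, section 2.9 says that "a 20% attrition rate was accounted for in both calculations". For the patients, "the final target for the patient group is set at 36 participants", partly to match the case–control component and partly to cover losses.

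The section concedes that the SD is large relative to the mean change. It answers this by noting that "our final target of 36 patients is considerably larger than the minimum required sample size of 24 derived from these pilot estimates", and presents the surplus as deliberate protection against overdispersion and outliers. It concludes: "This sample size ensures sufficient statistical power for both the between-group comparisons at baseline and the within-patient longitudinal analysis of treatment effects".

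**The concern.** A mean change of about half its SD is a moderate paired effect, and 24 patients looked too few to detect it with 80% power in a two-sided test. This is the only sample-size justification for the primary clinical outcome. The power figure for the group × time interaction later in section 2.9 cannot stand in for it, because section 2.8 analyses the THI in tinnitus patients only.

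If 24 is too low, the surplus that the plan relies on to absorb heterogeneity, outliers and dropout is largely lost, and the comparison may miss its stated power at the attrition the plan itself assumes.

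**Working it through.** **Inputs (section 2.9).** Mean change 12.07; SD 23.28, read as the SD of the change; paired t-test; two-sided alpha 0.05; power 80%; attrition 20%; target 36.

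**Standardised effect.** d = 12.07 / 23.28 = 0.5185.

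**Attempt to reproduce 24.**

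- Normal approximation: n = (1.960 + 0.8416)² / 0.5185² = 7.849 / 0.2688 = 29.2, so 30.
- Exact paired t-test (noncentral t, n − 1 degrees of freedom, noncentrality d√n): the smallest n with at least 80% power is 32.
- One-sided 5% test: 25 by the exact method, 23 by the normal approximation. This comes near 24 but contradicts the two-sided test stated in sections 2.8 and 2.9.

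No two-sided calculation at 80% power gives 24 from these inputs.

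**Exact two-sided power by number evaluable.**

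| Evaluable patients | Power |
|---|---|
| 24 | 68.2% |
| 28 | 75.3% |
| 29 | 76.9% |
| 30 | 78.4% |
| 31 | 79.8% |
| 32 | 81.1% |
| 36 | 85.6% |

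**Attrition.**

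- From 36 recruited, 20% loss leaves 36 × 0.8 = 28.8, so power is 75.3% to 76.9%.
- To keep 32 after 20% loss, 32 / 0.8 = 40 must be recruited.
- For the case–control component the plan goes from 30 pairs to 36, which is multiplication by 1.2. On that convention 32 becomes 38.4, so 39, and 36 corresponds to 30 evaluable patients with 78.4% power.
- 36 exceeds 32 by 4 patients, so 80% power holds only up to 4 / 36 = 11% loss.

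**Alternative reading of the SD.** If 23.28 were the SD of scores at one time point, the SD of the change would be 23.28 × √(2(1 − r)), where r is the pre–post correlation. The plan gives no r, so a range is shown.

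| Assumed r | SD of change | n (exact, two-sided, 80%) |
|---|---|---|
| 0.3 | 27.5 | 43 |
| 0.5 | 23.3 | 32 |
| 0.6 | 20.8 | 26 |
| 0.63 | 20.0 | 24 |

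On this reading 24 needs r of about 0.63, an SD of change of about 20.

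**The case against.** The strongest counter-argument is the SD. For wave V the section says explicitly that its SD is that of the differences; for the THI it does not, and it attributes the size of the SD partly to baseline severity, which could describe a score rather than a change. With a correlation near 0.63, 24 would then be right. This possibility stands as a question for the authors. It does not rescue the text as written: the SD is paired with the mean reduction and compared with the mean change, no correlation is given, and section 2.9 says its approach avoids assumptions about the covariance of repeated measurements.

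The practical damage is limited, and this is fair. With 32 or more evaluable patients power reaches 80%. At 20% loss the shortfall is 3 to 5 points by the exact test, and less by the normal approximation (78.3% to 79.7% with 28 to 29 patients). The study calls itself exploratory and its findings preliminary. The figures also describe a complete-case paired t-test, whereas section 2.8 plans a repeated-measures ANOVA over three time points for the THI. They therefore check the sizing calculation and are not the power of the planned analysis. None of this makes 24 correct.

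It is tempting to suppose that the two sample sizes were swapped, because the normal approximation gives 24.04 for the wave V inputs (0.08 / 0.14) and 29.2 for the THI inputs. That is conjecture: 24.04 rounds up to 25, and the exact test gives 27 for wave V. The finding does not depend on it.

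**Conclusion.** The concern holds. Under the stated test and inputs, with 23.28 taken as the SD of the change, 32 evaluable patients are required; the stated 24 is 8 patients short and gives 68.2% power. The margin of 36 over the true minimum is 4 patients rather than 12 and does not cover the planned 20% attrition, after which power is 75% to 77%. The mismatch with 24 holds by both the exact and the normal calculation. The shortfall after attrition is clear by the exact test and marginal by the normal approximation. The claim of a conservative surplus for the primary clinical outcome is unsupported.

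**What to change.** Keep the target of 36 and correct section 2.9:

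- State whether 23.28 is the SD of the change or of the scores at one time point. If the latter, give the pre–post correlation assumed and the resulting sample size.
- If it is the SD of the change, replace 24 with 32 evaluable patients in both places, and report about 86% power if all 36 complete and about 76% after 20% loss.
- Remove the sentence that sets 36 against 24 and the one after it that presents the surplus as conservative oversampling.
- Bring the dependent statements into line: that 20% attrition is covered in both calculations, that power is sufficient for the within-patient analysis, and, in the last paragraph of the section, that the t-test sizes guarantee sufficient power.

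The cost is wording only. No patients are added and no analysis changes; the stated power becomes less favourable. Holding 80% power after 20% loss would instead mean recruiting 40 patients, which this correction does not require.

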##### Primary neurophysiological outcome

2.7.1.2

The primary neurophysiological outcome will be the change in ABR wave V latency from baseline to post-treatment.

Previous studies have suggested that alterations in ABR latency parameters may represent objective neurophysiological changes associated with tinnitus-related auditory dysfunction. Wave V latency was chosen because it exhibits the highest test–retest reliability among ABR parameters and is the most clinically robust and widely reported metric in human auditory brainstem assessment. Although wave I amplitude is mechanistically important and is discussed in the introduction as a candidate biomarker of cochlear synaptopathy, its variability is substantially influenced by individual anatomical factors, making it less suitable as a primary endpoint for sample size estimation.

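### The paired t-test sample sizes are not a conservative bound for the group × time interaction, and the >85% power figure has no stated definition of f or correlation

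*Protocol article*

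**What the plan says.** Section 2.7.1.2 states: "The primary neurophysiological outcome will be the change in ABR wave V latency from baseline to post-treatment". For the longitudinal ABR analysis, section 2.8 specifies a mixed-design ANOVA with two groups and two time points, and says: "The primary parameter of interest will be the group × time interaction effect".

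Section 2.9 sizes the study on two paired t-tests:

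- a baseline tinnitus–control difference in wave V latency of 0.08 ms, with an SD of pair differences of 0.14 ms;
- a within-patient THI reduction of 12.07 points, SD 23.28.

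Its closing paragraph then links these sizes to the interaction. It says that "the sample size calculations were conservatively based on simpler t-test frameworks" and that "mixed-design ANOVA generally provides equal or greater statistical power than pairwise" t-tests for time-related changes. It reports "post-hoc power calculations based on a moderate effect size" (f = 0.25), from which "36 participants per group provide >85% power at α = 0.05 with two groups and two time points". It concludes that "the sample sizes derived from the t-test assumptions represent a conservative lower bound that guarantees sufficient power even under the simplest analytical framework", and that the mixed ANOVA will add sensitivity to the interaction on top of this.

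**The concern.** A paired pre–post test in patients carries the sampling error of one mean change. The interaction carries the error of two, patients and controls. Unless the controls' change has no variance, the interaction is the harder test for the same mean difference. The paragraph argues the reverse and offers it as a reason why no separate interaction calculation was needed.

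This paragraph is also the only power justification for the primary neurophysiological test. If the interaction comes out null, a reader told that power was guaranteed may take it as evidence that ABR does not change. The documents do not support that reading, because no size of wave V change that the study could detect is given anywhere.

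**Working it through.** **Inputs.** From the article: 36 per group, two groups, two time points, α = 0.05, f = 0.25, 20% attrition, and 0.08/0.14 ms for the baseline wave V difference. Not in the article: the T0–T1 correlation ρ, the SD of change in wave V latency, and the definition of f. These are varied below as assumptions.

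**1. The stated >85%.** The interaction has an F test on 1 and 70 df.

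*Repeated-measures convention:* λ = f² × N × 2/(1 − ρ) = 0.0625 × 72 × 2/(1 − ρ) = 9/(1 − ρ).

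| assumed ρ | λ | power |
|---|---|---|
| 0 | 9.00 | 84.1% |
| 0.05 | 9.47 | 85.9% |
| 0.2 | 11.25 | 91.1% |
| 0.5 | 18.00 | 98.7% |

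Power reaches 85% at ρ of about 0.025, so the inequality is reproduced for any ρ at or above that.

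*f defined on change scores* (d = 2f = 0.5): λ = f² × N = 0.0625 × 72 = 4.5, power 55.3%. With λ = f² × (N − 2) = 4.375 it is 54.1%.

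**2. What f = 0.25 means in the repeated-measures convention.** In a 2 × 2 layout the difference in change is 4 × f × SD = 1.0 SD of a single measurement. An SD in ms can be derived from the 0.14 ms only by assuming a correlation r within matched pairs: SD = 0.14/√(2(1 − r)).

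- r = 0: 0.099 ms
- r = 0.3: 0.118 ms

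The moderate effect is therefore 0.099 to 0.118 ms, or 1.2 to 1.5 times the whole assumed baseline tinnitus–control gap of 0.08 ms.

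**3. Interaction against paired test.**

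- Variance of a one-group mean change: σ²/n.
- Variance of the difference between two mean changes, equal change variances: 2σ²/n.
- Hence λ = n × d² for the paired test and (n/2) × d² for the interaction.

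Illustration with d = 0.08/0.14 = 0.571. This is a baseline effect, borrowed only to show the direction and size of the loss:

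- n = 36: paired λ = 36 × 0.3265 = 11.76, power 91.5%; interaction λ = 18 × 0.3265 = 5.88, power 66.7%.
- For 80% power: 27 pairs for the paired test, 50 per group for the interaction.

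**4. What 36 per group can detect.** Solving λ = (n/2) × d² for 80% power gives d = 0.67 SD of change with 36 per group. With 29 per group (36 × 0.8 = 28.8) it is 0.75 SD. For 85% power the values are 0.72 and 0.80.

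**5. Why actual power in ms is unknown.** With an assumed single-measurement SD of 0.099 ms, SD of change = 0.099 × √(2(1 − ρ)). Interaction power with 36 per group is:

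| assumed ρ | SD of change (ms) | difference in change 0.04 ms | difference in change 0.08 ms |
|---|---|---|---|
| 0.5 | 0.099 | 39% | 92% |
| 0.7 | 0.077 | 59% | 99% |
| 0.8 | 0.063 | 76% | >99% |
| 0.9 | 0.044 | 97% | >99% |

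**The case against.** Several points on the other side stand.

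- The >85% is not an arithmetic error. Under the repeated-measures convention it needs only a trivial correlation, and nothing in the article shows that f was defined on change scores. SPSS is named for the analysis and PASS for the sample size, and neither settles the definition.
- A reader might apply the THI effect (12.07/23.28 = 0.518) to the interaction and report its power as a shortfall. That is not supported: section 2.8 analyses THI in patients only, so THI has no group × time test.
- A reader might likewise take 67% as the trial's actual power. That is not supported either. The 0.571 is a baseline case–control effect. Using 0.14 ms as the SD of change would mean that one person's two recordings correlate no better than recordings from two people matched on age and sex. Section 2.7.1.2 chose wave V latency for its test–retest reliability, although it gives no value.
- Read literally, the guarantee sentence refers to the t-test framework, and the equal-or-greater claim is qualified as general and about time-related changes. The same paragraph nevertheless carries both over to the interaction.
- The study calls itself exploratory, and section 3.1 calls its findings preliminary and hypothesis-generating. This lessens the risk of misreading a null result but does not correct the statement.

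None of this rescues the reasoning. Smaller change variance in controls than in patients would narrow the loss of power relative to the within-patient paired test, but could not turn it into a gain.

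**Conclusion.** The point holds as a fault in the stated justification. For the 2 × 2 interaction, the paired t-test sizes are not a conservative bound, and mixed ANOVA does not have equal or greater power than the within-patient paired test. With equal change variances the contrast variance doubles; in the illustration, 92% becomes 67%. Neither paired calculation addresses change in wave V latency: one is a cross-sectional difference, and the other is an outcome that controls do not have.

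The >85% is true or false depending on a definition and a correlation that the text leaves out: 84.1% at ρ = 0, 98.7% at ρ = 0.5, about 55% with f on change scores. Where it does hold, it refers to a difference in change of one full cross-sectional SD, which is hard to call moderate.

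A reader might infer that the trial is underpowered for its primary neurophysiological outcome. The documents do not show that: with a high retest correlation, power could be adequate even for 0.04 ms. What they show is a guarantee without support and an argument that runs the wrong way. The ms figures rest on assumed pair and retest correlations; the detectable differences in SD of change do not, but they assume equal change variances.

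**What to change.** Rewrite the closing paragraph of section 2.9:

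1. As applied to the interaction, delete the lower-bound claim, the guarantee, the equal-or-greater-power claim and the statement that ANOVA adds sensitivity.
2. State that change in wave V latency was not the basis of the sample size. Then say that the interaction is a two-sample comparison of change scores, for which 36 per group gives 80% power for a between-group difference of 0.67 SD of change, or 0.75 SD with 29 per group after 20% loss.
3. Either drop the >85% figure or give it with its definition of f and the assumed T0–T1 correlation.
4. Convert the detectable difference to ms only if a retest SD is available. The pilot described in section 2.9 is not said to include retests, so otherwise show a stated range of correlations. The controls' T0–T1 data can supply the SD later.
5. Report the interaction estimate with a confidence interval, so that a null result is read against its precision.

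The cost is wording only: sample size, endpoint and analysis are unchanged. The stated power becomes less favourable.
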